#### Concealment mechanism {16b}

Sequentially numbered, opaque, sealed envelopes (SNOSE) will be used to implement the allocation.

#### Implementation {16c}

An independent researcher will perform the generation of the allocation sequence and preparation of the sealed envelopes. Allocation (1:1) will be based on computer-generated randomization using a block size of 4 for sequence generation. FH will enroll participants and screen for eligibility. Hereafter, envelopes will be handed over to GL by the independent researcher, who will assign participants according to the allocation sequence.

### Assignment of interventions: blinding

#### Who will be blinded {17a}

The researchers analyzing the final data will be blinded.

#### Procedure for unblinding if needed {17b}

Not applicable as surgeons and patients will not be blinded.

### Data collection and management

#### Plans for assessment and collection of outcomes {18a}

BS and SU will be responsible for contacting the patients for follow-up visits to obtain the filled questionnaires. Laboratory markers and clinical characteristics (e.g., operation time, the hospital stay) are available from the hospital patient information system.

#### Plans to promote participant retention and complete follow-up {18b}

Patients will receive reminders on their preferred way (e.g., SMS, WhatsApp, telephone) in regular intervals discussed with each patient individually to improve the patient-doctor contact and retention to follow-up.

#### Data management {19}

The data acquisition and data management will be carried out as part of the study by BS and SU. The data evaluation and interpretation of the pseudonymized data will be carried out in the Loretto Hospital Freiburg, Germany. Data will be obtained from the in-house patient information system and pseudonymized at the Loretto Hospital, Freiburg, Germany, by applying a code to the data. The code is generated using the “encode” command in the STATA statistics software (Version 15, StataCorp. 2011, College Station, TX, USA) using a calculation process. The pseudonymized table contains an alphanumeric code generated from the patient identification number by a calculation process. Before this, the numeric patient identification number is converted from “numeric” to “string” format using the “tostring” command. The assignment table is stored in encrypted form in the Loretto Hospital in Freiburg and is only available to BS. The assignment table is encrypted using AES-256-bit encryption (Advanced Encryption Standard). With the pseudonymized table alone, no assignment to the patient’s personal data is possible without the aid of the assignment table.

#### Confidentiality {27}

At no time do third parties have access to the data. Every patient is informed about the storage and use of the data. The written consent of each patient included is obtained for the processing of the data for research purposes. The patient’s consent to the storage and processing of the data for research purposes is obtained for a specific study.

#### Plans for collection, laboratory evaluation, and storage of biological specimens for genetic or molecular analysis in this trial/future use {33}

Not applicable as only simple blood samples will be collected and directly analysis by the in-house laboratory.

### Statistical methods

#### Statistical methods for primary and secondary outcomes {20a}

Descriptive statistics will be applied to the data (mean, standard deviation, median, interquartile ranges, frequencies). The Shapiro-Wilk test will be used as a normality test. Normally distributed data will be analyzed using repeated measure ANOVA and paired *t*-tests, whereas non-normally distributed data will be analyzed using the Friedman and Wilcoxon tests. We will also generate and evaluate quotients of inflammatory parameters to evaluate their impact on PROMs. An initial screening of all outcome parameters will be performed with explorative statistical approaches and univariate analyses to evaluate which combination of parameters and quotients might be relevant for PROMs. A *p* < 0.05 will be considered significant.

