### Trial design {8}

We will perform a comprehensive cohort trial involving a randomized and a prospective non-randomized study arm, each including intervention (full-endoscopic surgery) and control (microsurgical decompression) groups (superiority framework). Patients who do not consent to be randomized will be assigned to the non-randomized arm. Figure 1 illustrates the study design.

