The Oswestry Disability Index (ODI) is a questionnaire for evaluating functional disorders caused by back pain. The German version published in 2006 [9], the ODQ-D (Oswestry Disability Questionnaire- German), is scientifically recognized, and researchers regularly use it in back pain studies. The questionnaire is divided into 10 sections, each with 6 possible answers with point values of 0–5 points. The most appropriate answer should be ticked. As a result, the number of points achieved is set in relation to the maximum number of points and given as a percentage. Based on the results, the following judgments are made: 0–20% equals minimal, 21–40% equals moderate, 41–60% equals severe, 61–80% equals crippled, and 81–100% equals bed-bound or patients exaggerating their symptoms. The ODI will be measured as the primary outcome. The following time points will be assessed for the ODI: preoperatively, immediately postoperatively, 24 h, 48 h, 3 weeks, 1 year, 2 years, 3 years, and 5 years postoperatively (see also participant timeline {13}). The main outcome time point will be the 1-year evaluation. There is no repeated measure design statistical comparison planned and the 1-year, 2-year, 3-year, and 5-year outcome will be evaluated separately to evaluate the effectiveness of the respective treatment constantly for patients.

The SF-36 (Short Form Health 36) consists of 36 questions and is a general health questionnaire that uses 8 different dimensions to make statements about the patient’s state of health. It includes statements about the following: vitality, physical functioning, bodily pain, general health perceptions, the physical role of functioning, social role of functioning, and mental health.

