#### Sample size {14}

The Institute for Medical Biometry and Statistics at the University of Freiburg, Germany, provided biometric advice. The sample size estimate of this confirmatory study (superiority study) is based on the primary target value “Oswestry Disability Index (ODI).” The ODI is the gold standard of patient-related outcome measures (PROMs) in patients after spinal surgery [9, 12].

Null hypothesis: H0: *T*-*S* = *δ*

Alternative hypothesis: Ha: *T*-*S* > *δ*

Test statistic: *Z* = (*d*-*δ*)/*sd*

*T*: full endoscopic therapy; *S*: microsurgical therapy (standard/control); *δ*: “clinically accepted limit of superiority”; *d*: true difference in the mean between the two groups; *sd*: standard error of *d*

Calculation of the sample size:$$N=2\times \frac{{\left({Z}_{1-\alpha }+{Z}_{1-\beta}\right)}^2}{\delta -{\delta}_0}\times {s}^2$$

*N* = number of cases per group; z1-α/1 − *β* = standard deviation for a one-sided 1-*α* or 1 − *β*; *δ* = true difference in the mean between the two groups; *δ*0 = clinically acceptable limit of the mean value difference (“relevance limit”); S2 = variance

With an expected difference *d* in the mean value between the two groups of *d* = 8 (maximum number of points 45 points in the ODI), an assumed standard deviation of *s* = 10, a clinically acceptable limit for the mean difference of *δ*0 = 4, a 5% level of significance (*α* = 0.05), an equivalent allocation to the groups (*k* = 1) and an assumed 10% drop-out rate, a number of cases of *n* = 87 per group, or a total of *n* = 174 is required to achieve a power of 80% (1 − *β* = 0.8).

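### No test named in the analysis section is explicitly the between-arm 1-year ODI comparison that the trial was sized for

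*Protocol article*

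**What the plan says.** Trial design {8} describes a parallel comparison, "each including intervention (full-endoscopic surgery) and control (microsurgical decompression) groups (superiority framework". Outcomes {12} names the endpoint ("The ODI will be measured as the primary outcome") and the visit ("The main outcome time point will be the 1-year evaluation"). The same paragraph adds "There is no repeated measure design statistical comparison planned" and has the yearly ODI results evaluated separately.

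Sample size {14} sets the hypothesis as T minus S, endoscopic against microsurgical, relative to a limit. It gives a statistic for it, "Test statistic: *Z* = (*d*-*δ*)/*sd", where d is the difference between the two group means and the denominator is its standard error.

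Statistical methods for primary and secondary outcomes {20a} then says "Normally distributed data will be analyzed using repeated measure ANOVA and paired *t*-tests". If normality is rejected, the section switches to ranks: "non-normally distributed data will be analyzed using the Friedman and Wilcoxon tests". A Shapiro-Wilk test decides between the two families, and "A *p* < 0.05 will be considered significant". The section does not mention an independent two-sample test, a contrast between arms at 1 year, or the limit of 4. It does not say which test serves which outcome.

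**The concern.** The two arms contain different patients, and no matching is described. A paired t-test or a Friedman test on repeated visits asks whether scores change over time in the same people. Wilcoxon is listed as the non-normal counterpart of the paired t-test, so it reads most naturally as the signed-rank test, which asks the same question. The one named method that could hold arm as a factor, repeated-measures ANOVA, is the kind of analysis that Outcomes {12} says is not planned for the ODI.

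An analyst who followed the section literally would report that patients improve after each operation. That is expected after surgery and does not bear on the trial's confirmatory question, which is whether endoscopic surgery is better than microsurgery by more than the limit. The Shapiro-Wilk switch adds a lesser problem, because the observed data would choose the primary test.

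**Working it through.** **1. Which test was the trial sized for?** Inputs from Sample size {14}: expected difference 8, limit 4, SD 10, one-sided α = 0.05, power 80%, 1:1 allocation, 10% drop-out.

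- Independent two-sample formula: n = 2 × (1.645 + 0.842)² × 10² / (8 − 4)² = 77.3, so 78 evaluable per group.
- With drop-out: 78 / 0.90 = 86.7, so 87 per group and 174 in total. This is the stated figure.
- The formula is printed with an unsquared denominator, which would give about 309 per group. The stated figure therefore came from the squared form.
- Power with 78 per group: SE = 10 × √(2/78) = 1.60; Φ(4/1.60 − 1.645) = 80.3% (80.0% by noncentral t).

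The trial was sized for a comparison of two independent means against a limit.

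**2. Do the named tests address that comparison?**

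| Named in {20a} | What it compares | Tests T − S at 1 year against 4? |
|---|---|---|
| Paired t-test | two visits, same patients | No |
| Friedman | several visits, same patients | No |
| Wilcoxon (type not stated) | signed-rank: two visits, same patients; rank-sum: two arms | Signed-rank no; rank-sum only if the limit is built in |
| Repeated-measures ANOVA | visits, and arms if arm is entered | Only with a specified arm contrast at 1 year, and it conflicts with Outcomes {12} |

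**3. What would within-arm tests show?** The SD of change is not given, so it is assumed. With 78 patients, a two-sided paired t-test is significant once the mean change exceeds 1.991 × SD / √78:

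- SD of change 5: 1.1 points
- SD of change 10: 2.3 points
- SD of change 15: 3.4 points
- SD of change 20: 4.5 points

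A simulation of 4,000 runs assumed a baseline ODI of 40, an improvement of 20 in both arms, SD 10, a pre-post correlation of 0.5, 78 per arm and no true arm difference. Paired tests were significant in both arms in 100% of runs. The independent between-arm test (two-sided, against zero) rejected in 5.0%, its nominal rate. The within-arm results carried no information about the arm difference.

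**4. Does the repair change the sample size?** At one-sided 0.05 it does not: 78 evaluable and 87 enrolled per group. The significance rule in {20a} gives no sidedness. Read as two-sided, n = 2 × (1.960 + 0.842)² × 100 / 16 = 98.1, so 99 evaluable, 110 enrolled per group and 220 in total. With 78 per group, two-sided power is about 70%. The repaired text must therefore state the one-sided level.

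**5. What would baseline adjustment add?** With SE = 10 × √(2/78 × (1 − ρ²)), power against the limit rises from 80.3% to 83.5%, 86.0% and 89.2% for assumed baseline to 1-year correlations of 0.3, 0.4 and 0.5. The document gives no correlation. This is a gain in precision and does not measure the defect.

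**The case against.** The strongest reply is that the intent to compare arms is on paper. Sample size {14} prints a between-arm statistic with a limit, Trial design {8} sets intervention against control, and Outcomes {12} says pain scores of the study groups are compared. A repeated-measures ANOVA could carry arm as a between-subject factor, with an interaction or a contrast at 1 year. Wilcoxon could mean rank-sum, and a rank-sum test after shifting one arm by 4 would address the limit under a location-shift model. The statement ruling out repeated measures sits in the ODI paragraph, while {20a} covers all outcomes. These include blood samples taken three times (Intervention description {11a}), for which within-patient methods are natural. Finally, this is a journal article, and a fuller analysis plan may exist.

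Most of this stands as a limit on the claim. A reader might infer that the primary hypothesis is never tested at all, but the document does not support that: the statistic under Sample size {14} and the possible readings of ANOVA and Wilcoxon are enough to refuse it. It would also go too far to say that the ANOVA necessarily averages 1 year with the early visits, that no rank test can address a limit, or that baseline ODI is unused.

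The objection does not rescue the section. The ANOVA reading, applied to the ODI, meets the contrary statement in Outcomes {12}. The rank-sum reading still needs a limit that {20a} does not mention. Reserving these methods for serial blood markers would leave the ODI with no named test. An unseen analysis plan does not cure this, because the section names tests that do not fit the question; a plan that followed it would inherit the problem.

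**Conclusion.** The point holds in this form: no test named in {20a} is explicitly a test of the between-arm difference in 1-year ODI against the 4-point limit, and the section conflicts with Outcomes {12} on repeated measures and with the hypothesis in Sample size {14}. It must be fixed, because it governs the trial's only confirmatory question.

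The exact reproduction of 87 per group rests only on figures in the document. The size of the consequence is illustrative: the paired-test thresholds depend on an assumed SD of change, and the simulation on assumed ODI values. The conclusion that within-arm tests do not address the arm difference depends on neither. The document does not say in so many words that the 174 are all randomised patients; that is assumed here.

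**What to change.** In {20a}, add a sentence for the primary outcome with these elements:

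- 1-year ODI in the randomised arm is compared between the endoscopic and microsurgical groups by an independent two-sample comparison of means. ANCOVA with baseline ODI as covariate is preferable, since baseline is already collected, but it is an efficiency gain and not the correction itself.
- The mean difference is reported with its confidence interval and tested against the limit of 4 at the one-sided α of 0.05 used in Sample size {14}.
- The direction is explicit. Higher ODI means more disability, yet the stated alternative is T − S above the limit, so the text must say whether T and S are scores or improvements.
- The scale is explicit. Sample size {14} refers to a maximum of 45 points, while Outcomes {12} reports a percentage of the maximum.
- The Shapiro-Wilk test does not choose the primary test.

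Keep paired, Friedman and repeated-measures analyses as descriptions of within-patient change or for serial secondary markers, say which test serves which outcome, and reconcile {20a} with Outcomes {12} and Sample size {14}. The cost is wording only: no new data, and 87 per group (174 in total) still stands at the one-sided level.

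### No stated analysis adjusts the 1-year ODI for the preoperative ODI, so the primary comparison gives up precision the trial already collects

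*Protocol article*

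**What the plan says.** Outcomes {12} states: "The ODI will be measured as the primary outcome". The schedule includes a preoperative value: "The following time points will be assessed for the ODI: preoperatively, immediately postoperatively, 24 h, 48 h, 3 weeks, 1 year", followed by the later years. It fixes the primary time point, "The main outcome time point will be the 1-year evaluation", and then says "There is no repeated measure design statistical comparison planned and the 1-year, 2-year, 3-year, and 5-year outcome will be evaluated separately".

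Statistical methods {20a} applies a Shapiro-Wilk test and then chooses between two families. On one branch, "Normally distributed data will be analyzed using repeated measure ANOVA and paired" *t*-tests. On the other, "non-normally distributed data will be analyzed using the Friedman and Wilcoxon tests". No covariate is named for any treatment comparison. The univariate analyses mentioned there are an exploratory screen of parameters and quotients against patient-reported outcomes. They do not adjust the treatment effect.

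Sample size {14} uses a one-sided two-group comparison of means with "an assumed standard deviation of" 10, an expected difference of 8 and a relevance limit of 4. It does not say whether the 10 is the SD of the 1-year score, of the change from baseline, or a residual SD.

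**The concern.** The preoperative ODI is the obvious prognostic covariate for the 1-year ODI, and the schedule provides it at no extra cost. Read together, the two sections leave no route by which it enters the primary group comparison. The ODI paragraph excludes a repeated-measures comparison, and paired *t*, signed-rank and Friedman tests compare time points within patients.

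This is separate from whether paired tests suit a two-group hypothesis. If the paired test were replaced by an independent two-sample test of the 1-year ODI, the baseline would still be unused.

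The room for success is narrow. An expected difference of 8 against a limit of 4 leaves 4 points, at a planned power of 80%. Randomisation is in blocks of 4 with no stratification stated, so balance in preoperative ODI is left to chance. Adjustment would narrow the interval for the group difference and remove the part of it that is due to chance imbalance.

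**Working it through.** **Inputs from Sample size {14}:** expected difference 8, limit 4 (net 4), SD 10, one-sided α = 0.05, power 80%, 1:1 allocation, drop-out 10%. **Assumed:** the correlation ρ between preoperative and 1-year ODI, which the documents do not give, and that the SD of 10 is that of the raw 1-year score.

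**Step 1: the plan's own figure.** n = 2 × (1.645 + 0.842)² × 10² / (8 − 4)² = 77.3, rounded up to 78 evaluable per group. 78 / 0.9 = 86.7, rounded up to 87 per group and 174 in total. This matches the plan. (The printed formula lacks the square on the denominator and would give about 309 per group; the stated 87 follows from the squared form.) The figure is that of an unadjusted two-group comparison with the full SD of 10.

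**Step 2: unadjusted power.** The standard error of the difference is 10 × √(2/78) = 1.60. Power = Φ(4/1.60 − 1.645) = 80.3%.

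**Step 3: power with ANCOVA.** The residual SD is 10 × √(1 − ρ²), so power = Φ(4 / [10 × √((1 − ρ²) × 2/78)] − 1.645). The 90% interval half-width is 1.645 × residual SD × √(2/78). The equivalent unadjusted size is 78 / (1 − ρ²).

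| Assumed ρ | Residual SD | Power | Gain (points) | 90% half-width | Equivalent evaluable per group |
|---|---|---|---|---|---|
| 0 | 10.00 | 80.3% | – | 2.63 | 78 |
| 0.2 | 9.80 | 81.7% | 1.4 | 2.58 | 81 |
| 0.3 | 9.54 | 83.5% | 3.2 | 2.51 | 86 |
| 0.4 | 9.17 | 86.0% | 5.7 | 2.41 | 93 |
| 0.5 | 8.66 | 89.2% | 8.9 | 2.28 | 104 |
| 0.6 | 8.00 | 93.0% | 12.7 | 2.11 | 122 |

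At ρ = 0.1 power is 80.7%, a gain of less than half a point. The gain reaches 5 points from ρ of about 0.38. Noncentral-*t* versions of the powers are 0.2 to 0.3 points lower.

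**Step 4: would change from baseline do instead?** If the SDs at baseline and 1 year are equal (an assumption; the documents give no separate SDs), the variance of the change is 2(1 − ρ) times that of the raw score. Power is then 68.0% at ρ = 0.3, 73.7% at 0.4, 80.3% at 0.5 and 87.5% at 0.6. That is worse than ignoring the baseline below 0.5, and below ANCOVA at each of these values.

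**Step 5: chance imbalance.** If the preoperative SD is also 10 (an assumption), the chance difference between groups in mean preoperative ODI has a standard error of 10 × √(2/78) = 1.6 points, against a net difference of 4.

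**The case against.** The strongest reply is that this is a condensed article, that covariates are commonly left to the analysis plan, and that the article never says the comparison will be unadjusted. Silence alone would indeed be no finding. But the section is not silent: it names the tests for the primary and secondary outcomes, and none of them yields an adjusted group difference. An analysis plan with ANCOVA would depart from that list.

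A second reply is that repeated-measures ANOVA can take the preoperative value as a time level. It can, but Outcomes {12} excludes a repeated-measures comparison for the ODI, so this reading needs one section to override the other. Even then, the group-by-time contrast between baseline and 1 year is a change-score comparison, with the limits shown in step 4.

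Third, nothing is unmet under the plan's own inputs, since the unadjusted comparison reaches 80.3% against a target of 80%. That stands. A reader might infer that the sample size is wrong or that the randomised comparison is biased. Neither follows: the stated 87 reproduces, and the type I error of an unadjusted randomised comparison already allows for chance imbalance.

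Fourth, the size of the gain depends on a correlation that is not in the documents, and at low values it is small. That also stands. So does the ambiguity of the SD. If 10 were already a residual SD, the powers in the table would not apply, but the trial would then need the adjustment to reach its planned power. For example, at ρ = 0.5 the raw SD would be 10/√0.75 = 11.5, and unadjusted power Φ(4/[11.5 × √(2/78)] − 1.645), about 70%.

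Finally, a reader might infer that VAS, SF-36 and the blood markers share the gap, or that the rank tests cannot use the baseline at all. The documents do not support either. The exclusion of repeated measures sits in the ODI paragraph, so for the other outcomes repeated-measures ANOVA remains available with the preoperative value as a time level. Friedman and signed-rank tests can also include that value, although they do not adjust a group difference for it.

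**Conclusion.** The point holds for the 1-year ODI, as a recommended improvement and not as an error that invalidates the design. The preoperative ODI is collected, the stated methods provide no baseline-adjusted group difference, and the one method that might have used the baseline between groups is excluded for this outcome. The consequence is lost efficiency and avoidable sensitivity to chance baseline imbalance.

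The absence of adjustment is certain from the text; the size of the benefit is not. It runs from 1.4 power points at a correlation of 0.2 to 12.7 at 0.6, provided that the SD of 10 is the raw 1-year SD.

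**What to change.** In Statistical methods {20a}, state the primary analysis as an ANCOVA in the randomised arm: 1-year ODI on treatment group, with preoperative ODI as a continuous covariate. Test the adjusted group difference against the relevance limit in Sample size {14} and report its confidence interval. Keep this model whatever the Shapiro-Wilk result, using robust or bootstrap standard errors if residuals are skewed, and do not switch to rank tests. Use the same model for the separate evaluations of the later ODI time points, and bring Outcomes {12} and Statistical methods {20a} into line on repeated measures. State which SD the 10 represents. Leave the sample size unchanged, because the correlation is unknown.

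The cost is one paragraph, one degree of freedom and a simple fill-in rule for missing preoperative values so that those patients stay in the model. No extra patients, visits or measurements are needed. The change should be fixed before any 1-year results are examined by group.

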#### Outcomes {12}

Primary target variables:

Patient-related outcome measures (PROMs):Oswestry Disability Index (ODI)

Secondary target variables:Health questionnaire SF-36Pain intensity using the visual analog scale (VAS)Duration of the hospital stay (in days)Postoperative complicationsDuration of opioid useOperating time (in minutes)Re-admission within 3 weeks, 1 year, 2 years, 5 years postoperativelyBlood parameters for evaluating muscle damage:Creatine kinase (CK)Glomerular filtration rateMyoglobin (Mb)Erythrocyte sedimentation rateCreatine kinase: aspartate aminotransferase quotientProcalcitonin (PCT)C-reactive protein (CRP)White blood cell count (WBC)Interleukin (IL)-6

Renal parameters (e.g., creatinine clearance, glomerular filtration rate) will be measured to assess the influence of renal function on outcome measures, as creatinine kinase levels and myoglobin levels might be influenced by renal function. The severity of pain is determined using the visual analog scale (VAS). The scale is a 10-cm-long straight line, at the ends of which the extreme points of the pain to be measured are noted (0 cm = no pain, 10 cm = worst imaginable pain). The patient is asked to mark the intensity of his pain on the line with a pen [8].

The VAS is collected on the examination days before treatments (e.g., physiotherapy) are carried out. To assess the change in pain symptoms in the patients, the VAS values of the study groups at the time of the examination are compared and compared with statistical methods. The minimal clinically relevant reduction is given for input values above 30% [8].

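### Section {20a} lists paired or repeated-measures tests and no clear two-sample test for the 1-year ODI, which conflicts with sections {12} and {14}

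*Protocol article*

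**What the plan says.** All places are in the protocol article.

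- **Statistical methods for primary and secondary outcomes {20a}.** Outcomes are first checked with the Shapiro-Wilk test. The rule for the normal case is "Normally distributed data will be analyzed using repeated measure ANOVA and paired", where the last word refers to the t-test. The rule for the other case is that "non-normally distributed data will be analyzed using the Friedman and Wilcoxon tests". The only other analyses mentioned are descriptive statistics, quotients of inflammatory markers, and exploratory or univariate screening of which parameters bear on the patient-reported outcomes. No unpaired t-test, Mann-Whitney test, ANCOVA or regression with a treatment term is named.
- **Outcomes {12}.** The ODI is primary. "The main outcome time point will be the 1-year evaluation". On the same outcome: "There is no repeated measure design statistical comparison planned", with the yearly results evaluated separately.
- **Sample size {14}.** The study is called confirmatory, with superiority as its aim. The hypotheses concern T-S (full endoscopic minus microsurgical), the statistic is Z = (d-δ)/sd, and the planning quantity is the "true difference in the mean between the two groups". The inputs are d = 8, δ0 = 4, s = 10, α = 0.05 with one-sided quantiles, 80% power and 10% drop-out, giving 87 per group and 174 in total.
- **Trial design {8} and Sequence generation {16a}.** Each patient has one technique. Allocation in the randomised part is 1:1 in blocks of 4, with no matching.

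**The concern.** A paired t-test needs two linked values per unit. Here the only natural link is a patient's own earlier value, so the test asks whether patients changed after surgery. The trial asks something else: whether endoscopic patients end up better than microsurgical patients. Section {20a} is where an analyst would look for the primary test, and for a normally distributed ODI it offers two methods. One of them, repeated-measures ANOVA, is excluded for the ODI by {12}. What remains is the paired t-test.

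At stake is the confirmatory claim. An analyst following {20a} literally would report improvement within each group, which is expected after either operation and says nothing about their difference. An analyst following {14} would run a different test. The document does not say which section governs.

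The mismatch also reaches secondary outcomes that have one value, or one yes/no status, per patient at each analysis: hospital stay, operating time, opioid duration, complications and re-admission. For these there is no second value to pair.

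**Working it through.** **1. Which test does the sample size assume?** All inputs are from {14}: d = 8, δ0 = 4, s = 10, one-sided α = 0.05, power 0.80, drop-out 10%.

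For two independent groups, n = 2 × (z₁₋α + z₁₋β)² × s² / (d - δ0)².

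- One-sided: (1.645 + 0.842)² ≈ 6.183. n = 2 × 6.183 × 100 / 16 = 77.3, so 78 per group. 78 / 0.9 = 86.7, so **87 per group and 174 in total**. This is the stated figure.
- Two-sided with the same margin: 99 per group, 110 with drop-out. No match.
- Denominator not squared, as the formula is printed: 2 × 6.183 × 100 / 4 ≈ 309 per group before drop-out. No match.
- No margin (difference of 8 against zero): 20 per group one-sided, 25 two-sided. No match.

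Of the variants tried, only the independent two-sample, one-sided test against a margin of 4 gives 87. The size of the trial therefore rests on a test that {20a} does not list.

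**2. What do within-group paired tests show?** The SD of 10 is from {14}. Assumed for illustration: baseline mean 45, pre/post correlation 0.5, and improvements of 20 or 28 points.

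- SD of change = √(2 × 10² × (1 - 0.5)) = 10. SE with 78 patients = 10 / √78 = 1.13.
- Improvement of 20: 20 / 1.13 ≈ 17.7 standard errors. Improvement of 28: about 24.7. Both are far beyond any critical value.

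Simulation, 4,000 trials per scenario, 78 per group (the first three columns are two-sided tests at 5%):

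| Improvement, endoscopic / microsurgical | Paired test, endoscopic | Paired test, microsurgical | Two-sample test against 0 | One-sided two-sample test against margin 4 |
|---|---|---|---|---|
| 20 / 20 (no difference) | 100% | 100% | 4.4% | 0% |
| 28 / 20 (difference of 8) | 100% | 100% | 99.9% | 79.5% |

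The paired columns are the same in both rows, so they carry no information about the treatment contrast. The last column recovers the planned power.

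**3. Does naming the two-sample test change the sample size?** With 78 evaluable per group, SE = 10 × √(2/78) = 1.601 and 4 / 1.601 = 2.498. Power = Φ(2.498 - 1.645) = 80.3%, or 80.0% by the noncentral t distribution. The 87 per group stands.

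**The case against.** Several points can fairly be made for the plan, and they limit the concern.

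- **A reader might infer that the plan names no valid test anywhere, so that the superiority question would never be tested.** The document does not support that. Section {14} sets a between-group hypothesis on T-S, a test statistic and a margin. Section {12} also says that VAS values of the study groups will be compared. The defect is that {20a} does not carry over what {14} specifies.
- **A reader might infer that every named test is within-patient.** That is too strong. The type of Wilcoxon test is not given. Beside Friedman and opposite a paired t-test, signed-rank is the likelier reading, but rank-sum would be a valid between-group test. A repeated-measures ANOVA can also carry a group factor, and the exclusion in {12} sits in the ODI paragraph. For VAS, SF-36 or serial blood markers it could be a sound comparison, although {20a} mentions no group term.
- **A reader might infer that within-group p-values will be set against each other, or that unrelated patients will be paired.** Nothing in the document proposes either. Pairing unrelated patients at random would be arbitrary, but it would not by itself inflate the error rate.
- **This is a condensed article, and an analysis plan may exist.** Detailed test choice for each secondary outcome can reasonably be left to that plan. This does not answer the main point: {20a} names specific tests for the primary outcome, and those tests do not fit {12} or {14}.

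Even if Wilcoxon means rank-sum, a normally distributed 1-year ODI is still directed to a paired test.

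**Conclusion.** The concern holds in this limited form. For the primary outcome, {20a} lists paired or repeated-measures methods and no clear two-sample test. It contradicts {12}, which plans no repeated-measures comparison of the ODI, and it does not match {14}, whose one-sided between-group test with a margin of 4 underlies the 87 per group. This is a method stated wrongly, not a detail left out.

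Its importance comes from its place in the confirmatory analysis. The sample size is unaffected. The reproduction of 87 uses only the inputs in {14}. The simulation also rests on an assumed correlation of 0.5 and a large improvement in both groups; it illustrates that within-group tests cannot separate the techniques and does not predict this trial's results.

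**What to change.** Amend {20a}, and any analysis plan that follows it, as follows.

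- **Primary outcome.** State that the 1-year ODI is compared between the randomised endoscopic and randomised microsurgical patients as independent groups, by a two-sample t-test or an equivalent linear model with a treatment-group term. Report the mean difference with its confidence interval, and test it against the margin and with the sidedness set in {14}.
- **Non-parametric route.** If a between-group test is meant, name the Wilcoxon rank-sum test and say how the margin enters.
- **Repeated-measures ANOVA.** Reconcile it with {12}. If it is kept for outcomes other than the ODI, state the group factor.
- **Outcomes with one value or status per patient** (hospital stay, operating time, opioid duration, complications, re-admission). State that independent-group comparisons will be used. The specific test for each can go in the analysis plan.
- **Paired tests.** Keep them only as description of change within a group.

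The cost is a wording change. No new data or patients are needed, and the sample size stays at 87 per group.
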